#### Clinical Assessments During and After Treatment:

Clinical outcome measures will be assessed in the week prior to treatment, after each 5 sessions of treatment, then at 1, 4, and 12 weeks after treatment. These assessments can be completed over the phone if the participant is unable to attend the visit within the given time frame. The MADRS will be the primary

[figure not shown]

outcome measure and a score of greater than or equal to 18 will be used to establish eligibility. The HDRS-17 is the most commonly used outcome measure in previous randomized trials of rTMS and will be included for comparison purposes. However, the MADRS is well validated in LLD and has been used in trials of other interventions in TRLLD and will therefore be the primary measure. Secondary outcome measures will include the HDRS-17 and the self-rated QIDS16. The BSS will be administered after each 5 sessions of treatment, then at 1, 4, and 12 weeks post treatment as a safety measure to assess for suicidality.

To assess other potential predictors of response of rTMS we will assess anxiety, quality of life and medical burden. We will use the Brief Symptom Inventory – Anxiety, the Quality of Life Enjoyment and Satisfaction Scale (Q-LES-Q), and the Cumulative Illness Rating Scale for Geriatrics (CIRS-G).

### Cognitive Assessments

Cognition, in particular executive function and processing speed, are often impaired in LLD. It is an important predictor of acute antidepressant treatment outcome. Recent data from the first multi-centre RCT in TRLLD found that set-shifting performance is an important predictor of response with augmentation pharmacotherapy. rTMS may reduce the negative impact of executive dysfunction on treatment outcome through direct action on the DLPFC. The proposed battery has been used in other LLD clinical trials and there is normative data in depressed, anxious, and healthy elderly. Trained clinicians who are not neuropsychologists can administer the battery.

To assess executive function, we will be using 2 tests, the Delis-Kaplan Executive Function System (D-KEFS): Color-word interference, measuring behavioral inhibition, and the NIH Toolbox Flanker Inhibitory Control and Attention Test. These 2 tests measure distinct aspects of executive functioning. They can be repeated with limited practice effects. We will use the Test of Premorbid Function to provide an estimated premorbid-IQ. Memory will be assessed using the California Verbal Learning Test – second edition (CVLT-II).

Neuropsychological outcomes are not a primary focus of this study, but they are important clinical predictors and may be directly modified by rTMS, thus we will carry out the battery at baseline, after four to six weeks of treatment, and at twelve weeks following the final treatment session. Healthy controls will complete the cognitive battery for comparison at the screening appointment.

## **3.1.6 Interventions**

### *rTMS Treatment Procedures*

Following randomization and baseline MRI, patients will undergo neuronavigation, the target location will be specified by reverse coregistration from a stereotaxic coordinate on the standard Montreal neurological Institute (MNI-152) template brain, on to each individual's anatomical MRI. The MNI coordinates for L and R DLPFC will be [ $\pm 38$  y+44 z+26], drawn from a study identifying this site as optimal based on clinical outcomes and resting-state functional connectivity. rTMS will employ the MagPro X100/R30 stimulator equipped with the B70 fluid-cooled coil for DLPFC stimulation (MagVenture, Farum, Denmark). Neuronavigation will proceed using the *Visor 2* system (Advanced Neuro Therapeutics, Madison, WI) to position the coil for maximal field

[figure not shown]

strength at the left and right target region of the DLPFC for each individual subject. If a participant was unable to complete the MRI they are still able to undergo treatment using beam F3.

Prior to the first treatment, each subject's motor threshold (MT) will first be determined according to published methods during neuronavigated TMS over the primary motor cortex. Subjects will then undergo 20-30 sessions of rTMS, once daily on weekdays for 4 to 6 weeks. One study arm will undergo conventional sequential bilateral rTMS: R DLPFC stimulation at 120% resting motor threshold (RMT) at 1 Hz, in one train of 600 pulses over 10 min, followed by L DLPFC stimulation at 120% of RMT, at 10 Hz, in trains of 4 s with 26 s intertrain interval, for a total of 3000 pulses over 37.5 min. The second study arm will undergo cTBS of the R DLPFC at 120% RMT using bursts of 3 pulses at 50 Hz, bursts repeated at 5 Hz for a total of 600 pulses over 40 seconds, followed by iTBS of the L DLPFC at 120% RMT using bursts of 3 pulses at 50 Hz, bursts repeated at 5 Hz with a duty cycle of 2 s on, 8 s off for a total of 600 pulses over 3 min 9 s. Participants will be titrated to 120% RMT within the first four treatments to aid with tolerability. Subjects who cannot be titrated within 4 days will be allowed to continue in the study but the amount of time to reach the target intensity will be recorded in the treatment logs.

Common side effects of rTMS treatment are headache, discomfort and or pain at the stimulation site, facial muscle twitching, neck discomfort or pain, light-headedness or dizziness. These symptoms are expected and will be recorded separately from adverse events as side effects.

### 3.2 Data Collection and Statistical Considerations

#### 3.2.1 Power calculations for primary hypotheses

Power analysis for this study draws directly upon the preliminary clinical outcome data collected in our trials using sequential bilateral rTMS in older adults. We have chosen a non-inferiority delta of 2.75 points on the MADRS as the maximum acceptable difference between groups. According to the National Institute of Clinical Health and Excellence a clinically meaningful difference between drug and placebo is greater than 3 points on a depression rating scale. Based on data from the older adults in our two RCTs, the standard deviation of change has been 7.8 points. Setting the significance at 0.05 and the power at 80%, a sample size of 100 subjects per study arm, or **200 subjects** in total will be required to determine if cTBS then iTBS is non-inferior to 1Hz then 10 Hz DLPFC-rTMS. Based on 10% attrition a total of 220 subjects will be recruited. This *n* also provides a database for classifier training that is larger than any previous study in LLD.

#### 3.2.2 Data Collection and Management

RedCAP software will be used for data collection and overall study data management over the course of this project. RedCap is an open-source, web-based clinical data management and electronic data capture system and database. OCBN has deployed the RedCap Enterprise Edition at HPCVL, a fully supported commercial release with enhanced performance, security, validation, and quality assurance features. The system is developed and managed in compliance with HIPAA, PIPEDA, and FDA 21 CFR Part 11 regulations, providing functions such as defined user roles and privileges, user authentication and encryption, electronic signatures, de-identification of protected health information, comprehensive auditing features to record and monitor

[figure not shown]

access and changes to data, and a validated software development lifecycle. This system will be used to design electronic case report forms (eCRFs), data entry, data monitoring and cleaning, and for the query and export of datasets for statistical analysis and predictive modeling.

The forms created by the Temerty Centre for the purpose of collecting data from each subject and to track completion of assessments, MRI scans, and treatment sessions and will not contain any personal health information.

Research data gathered as part of this study may be shared and provided to other investigators affiliated with the Geriatric Mental Health Services (GMHS) for the purpose of data sharing. If participants are enrolled in multiple studies with the GMHS affiliated PIs, their research data will be shared across studies to reduce participant burden and avoid duplication of procedures. Only investigators/research teams affiliated with the PI will have access to secured files and/or research data and will be well-informed regarding the protection of participants' rights to confidentiality.

Furthermore, investigators collaborating with the study investigators (or other secondary investigators) will have access to de-identified research data collected during the study for the purposes of conducting secondary analyses about mental illnesses, such as autism spectrum disorder, depressive disorders, psychotic disorders, bipolar disorders, anxiety disorders, sleep disorders, or dementia (e.g., Alzheimer's disease). De-identified data from this study may be shared with the research community at large to advance science and health. We will remove or code any personal information that could identify participants before files are shared with other researchers to ensure that, by current scientific standards and known methods, no one will be able to identify participants from the information we share.

### 3.2.3 Outcome Analysis

**Objective#1:** Assessing non-inferiority of bilateral TBS based on change on the MADRS, an ANCOVA covarying for baseline differences will be used to measure the change at the final time point for each subject. This will be the primary clinical outcome measure.

Secondary outcome measures will include change from baseline to endpoint on the HDRS-17 and response and remission on the HDRS-17 and MADRS.

For categorical outcome measures, response will be defined as  $\geq 50\%$  reduction in symptoms on the HDRS-17. Remission will be defined as a HDRS-17  $\leq 10$  and a MADRS  $\leq 10$  at the week 4 or 6 final time point. Other secondary outcome measures will explore comparison of side effects between the two treatment arms, anxiety scales, quality of life scales and cognitive measures.

**Objective#2:** Outcome prediction from whole-brain rs-fMRI scans, data will be analysed using the FSL platform and in-house scripts to extract whole-brain regional connectivity matrices, followed by automated classifier training, using a support vector machine approach according to previously reported methodology. Based on preliminary data, classifiers will be trained on 4 features: whole-brain functional connectivity, region-wise betweenness centrality, and edge-wise functional connectivity variability. Automated classifiers will be trained and tested on the datasets for standard bilateral groups, with iterative cross-validation to ensure generalizability.

[figure not shown]

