### 3.1.4 Randomization and Blinding

Subjects will be randomized into the study, stratified by severity of treatment resistance (failure > 1 adequate trial). Degree of treatment resistance has been a major predictor of response to treatment in prior rTMS trials and it is essential to ensure that the groups are balanced with respect to this variable. The ATHF is a validated and reliable method of assessing adequacy of prior antidepressant treatment. We will also stratify the randomization by sites to ensure balance in the treatment condition across the two sites. We will randomize subjects based on a stratified randomization scheme using a random permuted block method. As the difference in duration between standard rTMS and TBS protocols is critical to the rationale of the study, it is not possible to blind the rTMS technicians or the patients to treatment assignment; however, since we believe there is equipoise between the two treatments and explain this to patients the expectancy effects should be minimal. **Raters** obtaining outcome measures **will be blind** to treatment assignment. All treatments will be conducted with minimization of personal contact (i.e., verbal communication) with the subject to reduce the impact of nonspecific therapeutic contact on outcomes.

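### The primary ANCOVA's covariates are left ambiguous and do not commit to the two randomisation factors; fixing them in advance costs nothing and can only help precision if the factors are prognostic

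*Protocol*

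**What the plan says.** Section 3.2.3 (Outcome Analysis) gives the primary analysis of MADRS change in one sentence: "an ANCOVA covarying for baseline differences will be used to measure the change at the final time point for each subject". The model is thus described only as "an ANCOVA covarying for baseline differences". The sentence names no covariate, and no other part of the protocol lists any.

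Section 3.1.4 (Randomization and Blinding) sets out a "stratified randomization scheme using a random permuted block method". One factor is prior treatment failure: patients are "stratified by severity of treatment resistance (failure > 1 adequate trial"). The reason given is that "Degree of treatment resistance has been a major predictor of response to treatment in prior rTMS trials" and that "it is essential to ensure that the groups are balanced with respect to this variable". The second factor is site: "We will also stratify the randomization by sites to ensure balance in the treatment condition across the two sites". The protocol makes no claim that site predicts outcome.

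Section 3.2.1 fixes the margin: "We have chosen a non-inferiority delta of 2.75 points on the MADRS as the maximum acceptable difference between groups". It sizes the trial at 100 per arm from a standard deviation of change of 7.8, significance 0.05 and power 80%. No gain from covariates is credited.

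**The concern.** The phrase on baseline differences is the only covariate rule for the one primary test, and it can be read in two ways.

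- **Narrow reading:** change in MADRS is adjusted for baseline MADRS. The stratification factors are then not in the model.
- **Literal reading:** the model adjusts for whatever differs between the arms at baseline. The covariates are then known only after the data are seen. Factors balanced by stratified blocks are also the least likely to be picked up.

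Either way, the factor whose balance the protocol calls essential has no assured place in the analysis. Two things are at stake. One is a modest amount of precision that the randomisation makes available. The other is discretion over the model in a test that decides non-inferiority. Many candidate covariates exist: section 3.1.5 names anxiety, quality of life, medical burden and cognition as possible predictors, and Table 1 schedules more than ten baseline measures.

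**Working it through.** **Inputs.** Margin 2.75, SD 7.8, 100 per arm, significance 0.05 and power 80% (section 3.2.1). Two stratification factors and permuted blocks (section 3.1.4). The share of variance that the factors explain, R², is not given, so a range is assumed.

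**1. The plan's own figure.** With a true difference of zero and one-sided 0.05:

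n per arm = 2 × (1.645 + 0.842)² × 7.8² / 2.75² ≈ 99.5, rounded up to 100.

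This reproduces the stated figure. One-sided 0.025 would need 127, so the calculation must be one-sided 0.05; the protocol does not state the sidedness, which is a separate matter. Power at 100 per arm:

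SE = 7.8 × √(2/100) = 1.103; power = Φ(2.75/1.103 − 1.645) = 80.2%.

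No covariate enters this, so the planned power does not depend on adjustment.

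**2. Gain from including the strata.** The residual SD becomes 7.8 × √(1 − R²). The half-width of the two-sided 90% interval is 1.645 × SE, and it narrows by 1 − √(1 − R²).

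| Assumed R² | Residual SD | Half-width (points) | Narrowing | Power |
|---|---|---|---|---|
| 0 | 7.80 | 1.81 | 0% | 80.2% |
| 0.02 | 7.72 | 1.80 | 1.0% | 80.9% |
| 0.05 | 7.60 | 1.77 | 2.5% | 81.9% |
| 0.10 | 7.40 | 1.72 | 5.1% | 83.7% |
| 0.20 | 6.98 | 1.62 | 10.6% | 87.3% |

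**3. Direction of the error if the strata are left out.** Stratified allocation already reduces the sampling variance of the arm difference. A model without the strata does not credit that reduction, so its standard error is too large. A simulation checked this with 200 patients, 2 × 2 strata of equal prevalence, blocks of 4 (block size is not stated, so assumed) and 6,000 runs per setting:

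| Assumed R² | One-sided error at the margin, without / with strata | Power at zero difference, without / with strata |
|---|---|---|
| 0 | 0.049 / 0.050 | 79.9% / 79.9% |
| 0.05 | 0.043 / 0.048 | 79.6% / 80.7% |
| 0.10 | 0.040 / 0.050 | 80.5% / 82.9% |
| 0.20 | 0.035 / 0.052 | 81.8% / 86.8% |

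The Monte Carlo standard error is about 0.003 for an error rate of 0.05, from √(0.05 × 0.95/6,000), and about 0.5 percentage points for power. Without the strata the error stays below 5% and power stays near 80%.

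**4. Would an imbalance rule select the strata?** In simulated trials of 220 patients (2 × 2 strata, equal prevalence, blocks of 4, 6 or 8, dropout 0% or 10%, all assumed), neither factor reached imbalance at p < 0.10 in any of 3,000 runs per setting. A literal imbalance rule would therefore in practice pass over both factors.

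**5. Open choice of covariates.** With 5 to 10 candidate covariates and joint R² of 0.2 to 0.3 (assumed; 4,000 runs per setting), the one-sided error at the margin was:

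- fixed model: 0.049 to 0.054;
- mechanical rule, adjusting for any imbalance at p < 0.10: 0.041 to 0.046;
- reporting the most favourable of baseline alone or baseline plus one other candidate: 0.075 to 0.087.

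Any harm comes from free choice among models, not from a mechanical imbalance rule.

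**The case against.** The strongest defence is that a full covariate list commonly belongs in the SAP, which is not shown, and that the sentence is about change in MADRS, so ordinary adjustment for baseline MADRS is a natural reading. The protocol describes no imbalance testing and no search among models. All of this stands. The point therefore rests on the wording that the protocol does contain, which leaves the model unclear, and not on missing detail.

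A reader might infer more from the text, in four ways that the documents do not support:

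- *The strata are excluded from the model.* The sentence names no covariates and rules none out. It fails to commit to the strata, and that is all.
- *The trial loses planned power, or its interval is wider than the design assumed.* The SD of 7.8 is unadjusted, so 80.2% is kept without the strata. What is forgone is a possible gain.
- *The primary test is invalid.* Leaving out prognostic strata makes a false claim of non-inferiority less likely, not more.
- *Covariates will be picked after the fact by someone who knows the allocation.* Patients and technicians are unblinded, but the raters are blinded and the analyst's access is not stated. The wording permits discretion without planning it. The inflation in step 5 needs selective reporting that the protocol nowhere describes.

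It is also fair to say that only treatment resistance is called prognostic. Site may add nothing.

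**Conclusion.** The point holds as a free improvement. The covariate rule for the primary test is ambiguous, and on neither reading does it secure the two randomisation factors. The gain in precision is modest and conditional: a 90% interval about 2.5% to 5% narrower, and power of 81.9% to 83.7% against 80.2%, if the factors explain 5% to 10% of the variance of change. That range is an assumption, and at R² = 0 there is no gain. Neither the planned 80% power nor the control of false non-inferiority claims is harmed by leaving the strata out. The second benefit does not depend on R²: with the terms fixed, the covariates of the single primary test are no longer open to choice after the data are seen.

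**What to change.** In section 3.2.3, replace the covariate phrase with:

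> an ANCOVA with treatment arm, baseline MADRS, treatment-resistance stratum (>1 vs not >1 failed adequate trial) and site as prespecified terms, whatever imbalance is observed

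Any SAP should carry the same list. The cost is one sentence and two degrees of freedom for the two stratification terms. Both factors are already recorded at randomisation, and the sample size does not change.

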#### 1.4.0 Objectives and Hypotheses

In summary, TBS has been shown to be effective in open-label studies of major depression. It has also been shown to have greater potency than conventional protocols in studies of motor physiology. However, to date there has been no direct comparison of the relative efficacy of these different forms of rTMS for TRLLD under randomized controlled conditions. This study will address the question of the relative efficacy of conventional versus theta-burst stimulation in the setting of TRLLD by comparing conventional HFL rTMS to TBS, while training and validating classifier algorithms for predicting treatment response using rs-fMRI.

[figure not shown]

**Objective 1:** To compare the effectiveness of a course of 4 minute sessions of TBS to a course of 45 minute sessions of conventional rTMS in LLD.

**Hypothesis 1:** Sequential bilateral forms of TBS will have non-inferior effectiveness compared to sequential bilateral conventional rTMS in older adults with depression.

**Objective 2:** To determine if an automated classifier can use pre-treatment resting-state fMRI, clinical and cognitive data to predict treatment outcome for both TBS and conventional rTMS.

**Hypothesis 2:** Patterns from whole-brain functional connectivity, obtained from pre-treatment rs-fMRI, will distinguish responders and nonresponders with >85% accuracy for TBS and standard rTMS.

**Exploratory Objective 1:** To compare network connectivity in depressed adults across the lifespan and rTMS-induced changes between bilateral and unilateral stimulation approaches using existing unilateral data in adults <60 from our group.

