Finally, the functional connectivity variability (FCV) will be calculated between each pair of regions in the 516-region atlas in each subject. FCV is a *dynamic* measure of functional connectivity, reflecting the stability of the correlation in activity between any two brain regions over the entire duration of the scan; a related approach is described in detail in Kucyi et al. 2013. To calculate FCV for a given pair of regions, a "sliding window" of data is established using the first 15 timepoints in each data series, and the Pearson's  $r$  correlation calculated for this window. The window is then advanced 1 timepoint, and the process repeated, until the window reaches the end of the 300-timepoint series. The result is a series of  $r$ -values reflecting the *evolving* functional connectivity between the two regions over time. The variance of this  $r$ -series is used as the FCV. We will also explore baseline FLAIR (to assess vascular burden) and diffusion tensor imaging (to assess white matter integrity) compared to healthy controls as vascular burden has been associated with depression in late-life.

In summary, the analysis methods will extract four kinds of feature maps for use in training automated classifiers for outcome prediction in each subject: i) a voxelwise map of correlation to the activity in the L and R DLPFC ROIs; ii) a whole-brain cross-correlation matrix of all 516 regions to one another; iii) BC values for each of the 516 regions; iv) FCV values for the cross-correlation of all 516 regions to one another over time.

[figure not shown]

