## Automated Classifier Construction

Training, testing, and cross-validation of automated classifiers will follow methods previously described for disease state classification using support vector machines (SVM). First, for each feature within the a given map, the Kendall tau rank correlation coefficient will be calculated as a non-parametric measure of the feature's relevance in discriminating responders from nonresponders. Next, features will be ranked according to discriminative power (i.e., absolute value of tau). Next, a leave-one-out cross validation approach will be used, omitting one subject per iteration during classifier training. Next, the set of consensus features (showing significant discriminative power across all 200 iterations) will be identified. This set of features will be used for construction and performance evaluation of the SVM. Classifier performance will be evaluated both in terms of overall accuracy and negative predictive value. The probability of obtaining the calculated performance under the null hypothesis will be determined using permutation testing, in which the class labels of the training data are randomly permuted and the training and cross-validation repeated, over 10 000 iterations, as previously described. SVM performance in discriminating responders from non-responders will be assessed by this method on each of the 4 feature sets described above. The performance of each classifier will be compared using the area-under-the-curve of the receiver-operating characteristic, chi-squared tests on overall accuracy and negative predictive value, and the decision-analytical approach of Vickers, which accommodates a spectrum of thresholds for pursuing or foregoing treatment.

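### The classifier plan has an unclear training set and tests against chance, so it does not evaluate Hypothesis 2's claim of more than 85% accuracy in each arm

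*Protocol*

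**What the plan says.** **Aim (Protocol 1.4.0).** Objective 2 asks whether a classifier "can use pre-treatment resting-state fMRI, clinical and cognitive data to predict treatment outcome for both TBS and conventional rTMS". Hypothesis 2 is narrower on predictors and numeric on performance. It begins "Patterns from whole-brain functional connectivity, obtained from pre-treatment rs-fMRI" and says that these "will distinguish responders and nonresponders with >85% accuracy for TBS and standard rTMS".

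**Training set (3.2.3 Outcome Analysis, Objective 2).** "Automated classifiers will be trained and tested on the datasets for standard bilateral groups, with iterative cross-validation to ensure generalizability". TBS is not named.

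**Cross-validation and test (Automated Classifier Construction).** Leave-one-out is used, omitting one subject each time, and consensus features are those that hold up over 200 iterations. Performance is summarised as overall accuracy and negative predictive value. Then: "The probability of obtaining the calculated performance under the null hypothesis will be determined using permutation testing". The other comparisons in that section (ROC area, chi-squared tests, decision analysis) set one classifier against another.

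**Predictors.** Outcome Analysis says "classifiers will be trained on 4 features: whole-brain functional connectivity, region-wise betweenness centrality, and edge-wise functional connectivity variability", which announces four and lists three. The neuroimaging section says "the analysis methods will extract four kinds of feature maps for use in training automated classifiers" and does list four, all derived from resting-state fMRI.

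**The concern.** The hypothesis is about each treatment and sets a bar of 85%. The stated analysis points to a single classifier on a set of patients that two sections describe differently, reports no accuracy by arm, and tests that classifier only against chance. A small permutation p-value could then be reported as support for Hypothesis 2 when it shows only that prediction beats random labelling.

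This matters because the Significance section builds on the claim: a reliable scan would spare non-responders futile treatment and raise response among treated patients to 90%. Separately, one of the two main objectives promises clinical and cognitive predictors that the classifier text never uses.

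**Working it through.** **1. Where 200 comes from.** Inputs from Protocol 3.2.1: margin 2.75, SD 7.8, alpha 0.05, power 80%. Per arm, n = 2(z_alpha + z_beta)² × SD² / margin². With one-sided 0.05: 2 × (1.645 + 0.842)² × 60.84 / 7.5625 = 99.5, so 100 per arm and 200 in total, as stated. (One-sided 0.025 gives 127 per arm and does not reproduce it.) Leave-one-out makes one iteration per subject, so 200 iterations means both arms together. Section 3.2.1 also presents the trial's whole sample as the training database.

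**2. Training set, side by side.** Outcome Analysis uses the word standard, which is elsewhere the label of the comparator (Hypothesis 2; section 3.1.4), but with a plural noun, and both arms are bilateral. Read literally, it means about 100 subjects and conflicts with 200 iterations. Read loosely, it means both arms in one pooled classifier. Neither reading gives training or accuracy by arm.

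**3. A pooled figure does not settle a claim about each arm.** 95/100 and 76/100 add up to 171/200 = 85.5%. The pooled figure is above 85% and one arm is well below it.

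**4. What the chance test requires.** The permutation threshold is approximated by the smallest count whose exact binomial upper tail is at most 0.05 (one-sided). The 50% row assumes balanced classes. The other rows use the share of the larger class as benchmark (assumed range). Section 1.1.2 cites response rates of 50-55% in other trials; the rate in this trial is unknown.

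| Benchmark | n = 200 | n = 100 |
|---|---|---|
| 50% | 113 (56.5%) | 59 (59%) |
| 60% | 132 (66%) | 69 (69%) |
| 70% | 152 (76%) | 78 (78%) |

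Every threshold is below 85%. With balanced classes, a classifier whose true accuracy is 70% passes with probability above 99% at n = 200 and about 99% at n = 100, although Hypothesis 2 is then false.

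**5. What 85% requires (100 per arm).** An observed 86/100 has an exact (Clopper-Pearson) 95% interval of 77.6% to 92.1%. The lower limit is 84.8% at 92/100 and 86.1% at 93/100, so 93 is the smallest count that clears the bar (binomial tail at 85%: 0.0275 for 92 and 0.0122 for 93). The probability of reaching 93 is:

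- 21% if true accuracy is 90%
- 45% if it is 92%
- 87% if it is 95%

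At one-sided 0.05, the level that reproduces the sample size, the bar is 92/100 and power at a true 90% is 32%. Pooled, the two-sided lower limit passes 85% from 181/200 (180/200 gives 84.98%).

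Section 3.1.1 lets patients who cannot tolerate the MRI be treated, so scans may be fewer. With 90 per arm (assumed), 84/90 is needed and power at a true 90% is 19%.

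All of step 5 treats leave-one-out predictions as independent, which is an approximation.

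**6. Predictors.** Objective 2 has three kinds: imaging, clinical and cognitive. Hypothesis 2 has one: connectivity. The feature sets have one: imaging. The mismatch is therefore with Objective 2 only.

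**The case against.** **TBS is not shown to be excluded.** A reader might infer from Outcome Analysis that TBS patients are left out. The documents do not support that. There is only one conventional arm, yet the phrase is plural. Both arms are bilateral, and the word may only separate them from the existing unilateral data in Exploratory Objective 1. The 200 iterations point to including TBS. What stands is that the two sections are not reconciled.

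**Imaging-only features fit Hypothesis 2.** A reader might take their use as a failure to test that hypothesis, but it names connectivity alone. Sections 3.1.5 and Cognitive Assessments do describe anxiety, quality of life, medical burden and cognition as predictors of response, and how they enter a model could be left to a SAP. The gap is between Objective 2 and the classifier text.

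**An accuracy estimate will exist.** Overall accuracy is to be computed and can be set beside 85%, so it would be too strong to say that the trial can neither confirm nor reject Hypothesis 2. A decision rule and reporting by arm could also be placed in a SAP. This has force as regards missing detail. It does not remove the mismatch: the protocol itself fixes the iteration count, the feature sets and the permutation null, and these do not answer the question that its hypothesis asks.

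**A rule based on the lower limit is demanding.** At a true 90%, both arms would clear 93/100 only about 4% of the time (0.206², taking the arms as independent). That is a fair warning. It is why restating the hypothesis is offered as an equal alternative.

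**Conclusion.** The point holds in this form. As written, the plan leads to a pooled accuracy and a test against chance, and neither evaluates more than 85% accuracy for TBS and for standard rTMS separately. The chance test is passed from 56.5% with balanced classes, or from 66% to 76% if the larger class is 60% to 70%, all at n = 200 and one-sided 0.05. The class shares are assumptions, because the documents give none for this trial.

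The pooled reading is inferred from leave-one-out with 200 iterations. It is well supported, but it is not stated in words. The omission of clinical and cognitive predictors is a separate, smaller mismatch with Objective 2.

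The MADRS non-inferiority comparison is not affected.

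**What to change.** 1. Reconcile Outcome Analysis with Automated Classifier Construction: name one training set that includes both arms, and make the iteration count follow from the scans available.
2. Report out-of-fold accuracy separately for TBS and for standard rTMS with a 95% interval, and judge Hypothesis 2 on that interval against 85%. Alternatively, restate Hypothesis 2 as better-than-chance prediction. Choose before outcomes are seen.
3. Repeat feature selection inside each fold. The consensus set is now chosen across all iterations and then used to evaluate performance, which would make accuracy by arm optimistic.
4. Keep label permutation for the chance comparison only, and say so.
5. Add a model with the baseline clinical and cognitive variables already collected, or narrow Objective 2 to imaging. Correct the feature list in Outcome Analysis so that it names four.

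Testing each arm's classifier in the other arm is optional; Hypothesis 2 does not need it.

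**Cost.** Wording and computing time, with no new data. The real price is that 85% becomes hard to establish: 93/100 per arm, with about 21% power per arm at a true accuracy of 90%. The sponsor should accept that openly or lower the claim.
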